**Discussion:**

The recruitment target of 485 was achieved, with a final recruitment total of 487. This trial is the largest definitive, pragmatic clinical and cost-effectiveness trial of cognitive behavioural therapy for people with schizophrenia whose symptoms have failed to show an adequate response to clozapine treatment. Using a prognostic risk model, baseline information will be used to explore whether there are identifiable subgroups for which the treatment effect is greatest.

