CBTp has the potential to help alleviate symptoms and improve quality of life in people meeting criteria for treatment-resistant schizophrenia and there are suggestions that it can help those who are not taking antipsychotics. However, there is insufficient research regarding CBTp for people with an inadequate response to clozapine or who are unable to tolerate the drug. The FOCUS trial aims to address the question of whether, Cognitive Behavioural Therapy (CBT) is clinically and cost effective and an acceptable treatment for people with confirmed treatment-resistant schizophrenia that is poorly responsive to an adequate trial of clozapine monotherapy (or unable to tolerate such a trial)? We will test the hypotheses that:In people with a diagnosis of schizophrenia spectrum disorder who have an inadequate response to or are unable to tolerate clozapine, CBTp plus Treatment As Usual (TAU) will lead to improvement in psychotic symptoms, measured using a psychiatric interview (PANSS), over a 21-month follow-up period compared with TAU alone.CBTp plus TAU will lead to improved quality of life and user-defined recovery compared to TAU alone.CBTp plus TAU will lead to a reduction in affective symptoms and negative symptoms compared to TAU alone.CBTp plus TAU will be cost effective compared to TAU alone.

In addition, we will develop a prognostic risk model that identifies baseline factors that predict good response to CBTp.

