### Sample size

As we intended to estimate treatment effects across a range of outcomes, including recovery, in addition to psychiatric symptoms, we powered the study to detect a generic effect size of 0.33. With 194 participants per group, using a t-test with a significance level of 0.05 we would have 90 % power to detect an effect size of 0.33. A target recruitment of 485 allowed for a dropout rate of 20 %.

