### Statistical analysis

Statistical analysis will take place after full recruitment and follow-up (i.e. there will be no interim analyses for efficacy, although an independent Data Monitoring Committee monitors trial progress and specifically any safety issues on a regular basis). The results of the trial will be presented following the standard CONSORT recommendations. Baseline and follow-up data will be summarised using the appropriate descriptive statistics and graphical summaries. Treatment effects will be presented with 95 % confidence intervals (CI). There will be no adjustment to secondary outcomes CIs for multiple testing. The primary outcome (PANSS total score at 21 months) will be analysed using a linear model that adjusts for pre-specified baseline covariates (baseline PANSS, sex, age) and includes a random effect for site. The development of treatment effects over time will be explored using a repeated measures mixed effects model that makes use of all available data, this assumes missing at random conditional on the observed covariates. The primary analysis will be intention-to-treat on available data (i.e. analyse as randomised). Secondary outcomes will be analysed in a similar way with generalised linear models appropriate for the distribution of the outcome.

We will try to identify subgroups for which the treatment effect is greatest using a prognostic risk model using baseline information. Response to treatment as measured by change in PANSS from baseline to 21 months will be explored in a general linear model. Covariates will include age; sex; baseline secondary outcome measures; childhood trauma; beliefs about self and others; working memory performance; and treatment allocated. Outcome analyses will be repeated excluding participants where the blind was broken to determine the robustness of the findings.

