Understanding and quantifying the risk of potential adverse effects of CBTp is important and early CBTp trials have been criticised for not giving this issue adequate consideration [59]. Klingberg et al. [60] have provided a useful template for assessing adverse effects as defined by the following criteria: (1) death by suicide, (2) suicide attempt, (3) suicidal crisis (explicit plan for serious suicidal activity without suicide attempt as defined by item 8, rating of 2 on the Calgary Depression Rating Scale for Schizophrenia; CDSS) and (4) severe symptomatic exacerbation (defined by the Clinical Global Impression Scale; CGI). We measure and report criteria 1–3 as part of National Research Ethics Committee requirements for recording and reporting serious adverse events. Additionally, we capture potential unwanted side effects from trial participation from scores on the CDSS and CGI. We will report scores of 6 or more on the GCI-Improvement Scale at 9 and 21 months’ follow-up. Furthermore, in order to capture the participants, own experiences and perspectives on trial participation we developed a bespoke measure of adverse effects from trial participation, which participants complete at the 21-month follow-up or are were offered at the point of withdrawal from the trial. Item generation was via a review of relevant literature on assessing adverse effects in psychotherapy trials [60, 61]. In relation to CBTp, we are also exploring the acceptability of CBTp through a qualitative evaluation of participants’ subjective experiences and perceptions of CBTp during the FOCUS trial. This aspect of the trial is led by service users.

It is unclear from the literature whether the treatment effects of CBTp may be greater for certain subgroups of people with a schizophrenia diagnosis. Such information would prove beneficial for people who have experience of psychosis and for their clinicians when making informed decisions about accessing CBTp. With this in mind, we seek to identify subgroups for which the treatment effect is greatest.

In summary, there an urgent need for evidence based treatments for people with a diagnosis of schizophrenia who are unable to tolerate or have experienced an inadequate response to clozapine. This trial addresses the question of whether CBTp is an effective treatment option for this group.

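### The model described for finding who benefits most from CBTp contains no allocation-by-factor term, so as described it shows prognosis and not differences in treatment effect

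*Protocol article*

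**What the plan says.** The aim appears in four places in the protocol article.

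- Statistical analysis: "We will try to identify subgroups for which the treatment effect is greatest using a prognostic risk model using baseline information".
- Abstract, Discussion paragraph: "baseline information will be used to explore whether there are identifiable subgroups for which the treatment effect is greatest".
- Main Discussion: "we seek to identify subgroups for which the treatment effect is greatest".
- Background, after the four hypotheses and as an addition to them: "we will develop a prognostic risk model that identifies baseline factors that predict good response to CBTp".

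The method appears once, under Statistical analysis. The outcome and model class are given as "Response to treatment as measured by change in PANSS from baseline to 21 months will be explored in a general linear model". The terms follow: "Covariates will include age; sex; baseline secondary outcome measures; childhood trauma; beliefs about self and others; working memory performance; and treatment allocated".

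The article describes no product term between allocation and a baseline factor, no separate model by arm, and no step that compares the treatment effect across levels of a risk score.

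**The concern.** Three of the four statements ask about effect modification: for whom is the difference between CBTp plus TAU and TAU alone largest? The Background statement, on predicting response to CBTp, is naturally read the same way. The described model answers another question. With allocation as one covariate among others, it estimates a single treatment effect and, separately, how each baseline factor relates to PANSS change in both arms together.

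The wording makes the two easy to confuse. The article treats within-person PANSS change as response to treatment, yet TAU participants change too. A factor that goes with improvement equally in both arms would have a clear coefficient in this model. Under the Background wording it could then be presented as a predictor of good response to CBTp. The main Discussion says the answer is meant to inform decisions by service users and clinicians about taking up CBTp. Such decisions need the difference between arms, not general prognosis.

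**Working it through.** **1. The plan's own figure.** The article gives no figure for the subgroup analysis, only for the main comparison, where the standardised difference is 0.33. It states the basis as "With 194 participants per group, using a t-test with a significance level of 0.05 we would have 90 % power to detect an effect size of" (the value just given). The inflation is stated as "A target recruitment of 485 allowed for a dropout rate of 20" (per cent). A two-sided two-sample t-test with SD 1 needs 193.94, so 194 per group, with power 90.0% at 194. Then 2 × 194 = 388 and 388 / 0.8 = 485. Both stated figures reproduce.

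**2. What the described model can show.** Let A be allocation (0 or 1) and X the baseline factors. With the listed terms entered as covariates,

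E(change) = b0 + b′X + tA.

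The treatment effect for a participant with profile X is E(change | A = 1, X) − E(change | A = 0, X) = t. X cancels, so the effect is t for everyone. This is algebra and does not depend on sample size. With a product term, E(change) = b0 + b′X + tA + c′(AX), the effect is t + c′X, and c carries the subgroup information.

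**3. Simulation check.** There were 2,000 trials of 388 participants, allocated 1:1, with residual SD 1. The true effect was 0 in about half of participants and 0.66 SD in the rest.

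- Listed terms only: one effect, mean 0.33 SD; the spread of predicted effects across participants was 0 in every run.
- With the product term: mean estimated difference in effect 0.65 SD (truth 0.66), detected in 90% of runs.

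**4. Precision once the term is added.** Assume a binary factor with prevalence p, N analysed, 1:1 allocation and SD 1. A subgroup of size Np has Np/2 per arm, so its effect has variance 2/(Np/2) = 4/(Np). The difference between the two subgroup effects has

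SE = √[4/(Np) + 4/(N(1 − p))].

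For N = 388 and p = 0.5: SE = √(4/194 + 4/194) = 0.203. This is twice the main-effect SE of √(2/194) = 0.1015. The difference detectable with 80% power at two-sided 0.05 is (1.960 + 0.842) × SE. Power for a difference of 0.33 SD is Φ(0.33/SE − 1.960).

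| N analysed | Prevalence | SE | Detectable difference (80% power) | Power for 0.33 SD |
|---|---|---|---|---|
| 388 | 50% | 0.203 | 0.57 SD | 0.37 |
| 388 | 30% | 0.222 | 0.62 SD | 0.32 |
| 388 | 20% | 0.254 | 0.71 SD | 0.26 |
| 487 | 50% | 0.181 | 0.51 SD | 0.445 |
| 487 | 30% | 0.198 | 0.55 SD | 0.385 |
| 487 | 20% | 0.227 | 0.64 SD | 0.307 |

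The two values of N are the number left after the planned 20% dropout and the full number recruited. The prevalences and the 0.33 SD interaction are assumptions; the article gives none. Adjusting for baseline PANSS would reduce the residual SD and improve every row.

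**The case against.** The strongest reply is that the article never says main effects only. A general linear model can hold product terms, the covariate list is introduced in a way that leaves it open, and a list of variables is not a model formula. The stated purpose is itself consistent with interactions. A risk model used to find subgroups could mean a baseline score followed by a comparison of effects across it. The article also links to a statistical analysis plan and a full protocol, neither of which is shown, where such terms would ordinarily be written. Finally, the work is exploratory: the article speaks of trying, exploring and seeking.

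Much of this stands. A reader might infer that the trial will be unable to identify any subgroup, or that prognostic factors will be reported as predictors of CBTp benefit. The documents support neither: the analysis finally run may contain the terms, and the article gives no reporting rule.

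What does not stand is that this is only detail left to another document. The article chooses an outcome, a model class and a set of terms, places allocation among the covariates, and pairs them with an aim that those terms do not address. No second step is mentioned.

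A reader might also infer that clozapine status at entry, inadequate response versus intolerance, is an obvious missing candidate factor. The text does not support that. The inclusion criterion makes no such two-way split, since discontinuation may be for adverse reactions or for lack of efficacy. The section on assessment of eligibility says that information on clozapine use was sought at referral, not that the reason for stopping was coded.

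**Conclusion.** The point holds for the model as described. That model yields one treatment effect for all participants, and its baseline coefficients are prognostic in both arms together. It therefore gives no information on where the effect of CBTp is greatest, and the Background wording invites prognostic factors to be read as predictors of benefit.

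This should be corrected, but it concerns an exploratory aim. The primary analysis, the sample size and the conduct of the trial are untouched. The conclusion on the model rests on reading the listed terms as main effects, which the unseen analysis plan may supersede. The precision figures (0.57 to 0.71 SD with 388 analysed, 0.51 to 0.64 SD with 487) describe what the trial could learn after the correction, not harm already done. They rest on an unadjusted SD of 1, two-sided 0.05, 80% power and assumed prevalences of 50% to 20%.

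**What to change.** State one of these two analyses, in the analysis plan if it is not already there:

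- 21-month PANSS modelled on baseline PANSS, site, allocation, the candidate baseline factors and allocation × factor; or
- a baseline risk score built blind to arm, then 21-month PANSS modelled on baseline PANSS, site, allocation, score and allocation × score.

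Report the interaction estimates with 95% confidence intervals as the evidence on subgroups, labelled exploratory. Label the main effects of baseline factors as prognostic only, and align the Background wording with that distinction.

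The cost is wording and a little more analysis, with no new data. The article states that data collection was continuing and that no interim efficacy analysis was planned, so the terms could still be fixed before the outcome analysis. The downside is imprecision: intervals will be wide, and an interaction that is not significant should not be read as evidence that the effect is the same in all subgroups.

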### Inclusion criteria

Patients were required to meet the following criteria to be eligible for enrolment:A criterion level of persistent symptom severity despite an adequate trial of clozapine in terms of dosage, duration and adherence [33]:Treatment of clozapine at a stable dose of 400 mg or more (unless limited by tolerability) for at least 12 weeks, or if currently augmented with a second antipsychotic that this has been given for at least 12 weeks, without remission of psychotic symptoms, or have discontinued clozapine due to adverse reactions (including agranulocytosis) or lack of efficacy in the past 24 months.Presence of at least one psychotic symptom with severity ≥4 (for hallucinations/delusions) or ≥5 (for suspiciousness/grandiosity) on the Positive and Negative Syndrome Scale (PANSS) in addition to a PANSS total score of at least 58, which is equivalent to a clinical global impression (CGI) of being at least mildly ill [34].Be in contact with mental health services and have a care coordinator.Either meet ICD-10 criteria for schizophrenia, schizoaffective disorder or delusional disorder or meet entry criteria for an Early Intervention for Psychosis service (operationally defined using PANSS) in order to allow for diagnostic uncertainty in early phases of psychosis.Aged at least 16 years’ oldCompetent and willing to provide written, informed consent.

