**Fig. 1 Fig1:**
[figure not shown]
Trial flow diagram

The primary outcome measure is the total PANSS score at 21-month assessment (12 months’ follow-up from the end of treatment). The primary outcome will allow for comparison with other published trials, inclusion of our results in any future systematic reviews and meta-analyses. Having the primary outcome at 12-month follow-up will allow an evaluation of the benefits of CBTp beyond the end of treatment. The PANSS is a 30-item rating scale designed to provide a comprehensive assessment of psychopathology in adult patients with schizophrenia. Five components have been reported: positive, negative, depression-anxiety, agitation-excitement, and disorganisation [35, 36]. The PANSS was completed at baseline assessment, 9-month follow-up and 21-month follow-up.

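### The exploratory response model analyses change in PANSS without adjusting for baseline PANSS total, so baseline severity measures can appear to predict improvement through regression to the mean

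*Protocol article*

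**What the plan says.** The Statistical analysis section describes two models for PANSS.

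The primary model takes the 21-month total score as outcome and "adjusts for pre-specified baseline covariates (baseline PANSS, sex, age) and includes a random effect for site".

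The response model takes a change score: "Response to treatment as measured by change in PANSS from baseline to 21 months will be explored in a general linear model". Its covariates follow: "Covariates will include age; sex; baseline secondary outcome measures; childhood trauma; beliefs about self and others; working memory performance; and treatment allocated". Age and sex carry over from the primary model, but baseline PANSS does not.

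The phrase about secondary measures does not bring baseline PANSS total back in, because the section on eligibility and outcome measures makes PANSS total the primary outcome: "The primary outcome measure is the total PANSS score at 21-month assessment (12 months’ follow-up from the end of treatment").

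The Background gives the model's purpose: "we will develop a prognostic risk model that identifies baseline factors that predict good response to CBTp". The Statistical analysis section words the aim differently: "We will try to identify subgroups for which the treatment effect is greatest using a prognostic risk model using baseline information".

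**The concern.** Change is the 21-month score minus the baseline score, so baseline PANSS enters the response with a minus sign. A participant whose baseline score is high, partly by chance, will on average fall back. Any covariate that tracks baseline PANSS inherits part of that fall and seems to predict improvement, unless baseline PANSS is itself in the model.

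The article's baseline measures include several likely to track it: PSYRATS, CDSS, CGI and PSP. The listed model would then tend to show more severely ill participants as better responders, even where these scales say nothing about the 21-month score beyond what baseline PANSS already says. Since the Background promises to identify baseline factors that predict good response, that pattern could be reported as a substantive finding.

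**Working it through.** **The plan's own figure.** The article states no figure for the response model. Its sample size supplies n, and it reproduces: an effect size of 0.33 with 194 per group at two-sided 0.05 gives power 0.900 by the noncentral t, and 388 / 0.80 = 485. The number analysed is taken as 2 × 194 = 388.

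**Assumptions, since the article gives no correlations.** Let B be baseline PANSS and F 21-month PANSS, with equal SDs scaled to 1. Let X be a baseline severity measure scaled to SD 1, with higher meaning worse; for a scale scored the other way the sign flips and the size stays. Let r = corr(B, F), from 0.4 to 0.6, and q = corr(X, B), from 0.3 to 0.7. X is given no information about F beyond B, so corr(X, F) = qr.

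**Slope of change on X without B in the model**

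- Slope = cov(X, F − B) = qr − q = −q(1 − r)
- Residual variance = (2 − 2r) − slope²
- SE = √(residual variance / 388)
- R² = slope² / (2 − 2r)

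| r | q | Slope | Residual variance | SE | z | R² |
|---|---|---|---|---|---|---|
| 0.6 | 0.3 | −0.12 | 0.7856 | 0.045 | −2.7 | 1.8% |
| 0.5 | 0.5 | −0.25 | 0.9375 | 0.049 | −5.1 | 6.2% |
| 0.4 | 0.7 | −0.42 | 1.0236 | 0.051 | −8.2 | 14.7% |

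A negative slope means a larger fall in PANSS for those worse at baseline. The true value, given B, is zero in every row.

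**Simulation of one covariate plus treatment** (388 participants, 1,000 runs per setting; r of 0.4, 0.6 and 0.7; q of 0.3, 0.5 and 0.7). X is significant at 5% in 61% to 100% of trials without B. With B in the model this falls to about 4% to 7%, and the mean coefficient is about zero.

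**Simulation of five severity measures entered jointly** (mutual correlation 0.3; q of 0.3 or 0.5; the same r). Each is falsely significant in 16% to 67% of trials, and at least one in 63% to 100%. With B added the figures are about 5% each and 21% to 25% for at least one. The latter is close to what five independent 5% tests would give (1 − 0.95⁵ = 23%).

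**Treatment-by-X interaction.** In the single-covariate simulation it is falsely significant in about 4% to 6% of trials, with or without B. Regression to the mean acts alike in both randomised arms.

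**The case against.** The best defence is that the covariate list is open-ended, the analysis is exploratory, and the article links an intention-to-treat analysis plan that is not shown. That plan may name baseline PANSS. But the article does more than leave a detail out: it fixes a change score and a covariate list, and names baseline PANSS for the primary model nearby. The defence limits the weight of the point without answering it.

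Other limits stand:

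- **Size.** It rests on assumed correlations. At q = 0.3, with r from 0.4 to 0.7, the spurious R² is only about 1% to 3%. The z values are for one covariate alone, whereas the article describes many entered together. Calling the false predictors strong would go beyond the documents.
- **Entry threshold.** Eligibility requires a "PANSS total score of at least 58, which is equivalent to a clinical global impression (CGI) of being at least mildly ill", judged on the same baseline assessment, and a reader might infer that this selection worsens the artefact. Selection can increase the average fall in the whole sample, but it weakens the slope of a correlated covariate. With r = 0.6 and q = 0.5, cutting the baseline distribution at −1.5 SD moves the simulated slope from −0.20 to −0.16. Over all settings the false-positive range goes from 61%–100% to 42%–100%.
- **PANSS components.** Some might count as secondary outcomes and so enter the model. A reader might infer that this would cure only part of the problem. If the components entered sum to the total, the adjustment is complete; if only some enter, it is partial. The article does not say which enter, so neither can be asserted.

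**Conclusion.** The point holds for prognostic main effects. As listed, the response model would tend to credit baseline severity measures with predicting improvement when they carry nothing beyond baseline PANSS. For one covariate alone the spurious slope is 0.12 to 0.42 SD per SD (z about 2.7 to 8.2). This assumes r of 0.4 to 0.6, q of 0.3 to 0.7, equal SDs and 388 analysed. Per covariate it is less when several are entered jointly.

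A reader might infer that the subgroup treatment effects, or the trial's main result, are biased too. The documents do not support that. The randomised comparison and treatment-by-covariate interactions are untouched, and the primary model already adjusts for baseline PANSS. The exposure arises because the listed model names only main effects, and these bear on the Background's aim of finding predictors of good response. The model should be corrected before it is fitted, but the omission does not threaten the trial's conclusion on efficacy.

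**What to change.** State that the response model takes 21-month PANSS total as outcome with baseline PANSS total as a mandatory covariate, in line with the primary model. Keeping the change score is equally good provided baseline PANSS total is always in the model: the coefficients of all other covariates are then identical, and only the baseline coefficient shifts, by exactly 1.

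The cost is one line in the analysis plan and one degree of freedom. No new data are needed, because PANSS was scored at the baseline assessment to determine eligibility. If the analysis plan already includes the term, only the article's description needs aligning.

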We will also address the influence of compliance and the therapeutic alliance between therapist and participant via causal or ‘mediation’ models. Traditional approaches to mediation [54] assume that confounding between the putative mediator and clinical outcome is absent (i.e. there is no omitted variable bias). We will compare the results of three sets of assumptions: (a) no confounding, (b) that we have measured and are able to adjust for all important confounders [55], and (c) that we are able to effectively adjust for unmeasured confounders (hidden confounding) using instrumental variable-based methods, specifically analyses based on principal stratification [56].

The sensitivities of all treatment effect estimates to missing outcome data will be explored; these models will explore the robustness of the treatment estimates to whatever small amount of missing data there is. The following strategy will be followed: firstly, the main analysis will use all available data that we believe are valid under the assumption of missing at random; secondly, a suite of sensitivity analysis to explore the robustness of the primary analysis to departures from assumptions that includes all randomised participants; finally, if required, sensitivity analyses will include multiple imputation, and imputing a range of values for missing data under missing not at random assumptions [57].

Data missing at baseline will be reported as such. If required for models for primary or secondary outcomes, continuous data will be imputed with the centre specific mean of that variable, missing binary/categorical data will include a missing indicator.

A copy of the intention to treat statistical analysis plan can be found here: http://w3.abdn.ac.uk/hsru/CHaRT/public/content/ShowPage.aspx?page=statistical-analysis-plans.

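### The centre-mean and missing-indicator rule for baseline data is sound for the randomised comparisons but should not extend to the exploratory PANSS response model or mediation set (b), as its wording allows.

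*Protocol article*

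**What the plan says.** All the relevant text is in the protocol article, under Statistical analysis.

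- **Baseline rule.** Where models of the primary or secondary outcomes need it, "continuous data will be imputed with the centre specific mean of that variable, missing binary/categorical data will include a missing indicator". No other rule for incomplete baseline covariates is given. Multiple imputation appears only as an optional sensitivity analysis for missing outcome data.
- **Primary model.** PANSS total at 21 months, adjusted for baseline PANSS, sex and age, with a random effect for site.
- **Response model.** "Response to treatment as measured by change in PANSS from baseline to 21 months will be explored in a general linear model". The covariates are age, sex, the baseline secondary measures, childhood trauma, beliefs about self and others, working memory and allocation.
- **Mediation and compliance models.** Results are compared under three sets of assumptions. Set (a) is no confounding. Set (b) is "that we have measured and are able to adjust for all important confounders". Set (c) handles hidden confounding by instrumental-variable methods based on principal stratification.

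The rule names neither the response model nor the mediation models. A separate intention-to-treat analysis plan is cited but is not available here.

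**The concern.** Filling a covariate with its mean is harmless when the coefficient of interest is randomised allocation, because allocation is independent of every baseline variable. It is not harmless when the coefficient belongs to another baseline factor or to a mediator. A participant given the centre mean contributes no adjustment for that covariate, so part of the covariate's effect is credited to whatever correlates with it.

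The response model and set (b) both interpret such coefficients. Both also draw on the variables most likely to have gaps. Baseline PANSS and age are eligibility criteria and should be nearly complete, whereas the response model uses many scales, and the article says that assessments are ordered so that the most important measures are collected first. The Background states the aim of finding baseline factors that predict good response to CBTp, and the Discussion says that such information would help patients and clinicians to decide. At stake is whether a factor or a mediator is reported as influential only because another variable was incompletely recorded.

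**Working it through.** **1. The plan's own figure.** The only figure the article gives here is the sample size. For an effect of 0.33, two-sided 5% (sidedness is not stated) and 90% power, n = 2(1.960 + 1.282)²/0.33² ≈ 193 per group by the normal approximation. The noncentral t gives 194 (power 0.9001), matching "With 194 participants per group". Then 388/0.80 = 485, the stated target. The figure reproduces, and 388 is used below as the number analysed.

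**2. Assumed inputs.** The article gives no missing rates, correlations or covariate effects, so these are assumptions:
- confounder C, standardised, effect β = 0.4 SD on the outcome;
- predictor or mediator X with no effect of its own, correlation ρ = 0.5 with C (given allocation);
- C missing completely at random in a fraction p and replaced by the centre mean, five centres.

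**3. Bias formula.** After mean-filling (ignoring true differences between centres), Var(C\*) = 1−p, Cov(C\*,X) = (1−p)ρ and Cov(C\*,Y) = (1−p)β. With Cov(X,Y) = ρβ, least squares gives X the coefficient

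bias = ρβ·p / [1 − (1−p)ρ²].

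With no adjustment the bias would be ρβ = 0.20. At p = 0.20 it is 0.20 × 0.20/(1 − 0.80 × 0.25) = 0.04/0.80 = 0.05, a quarter of the confounding.

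**4. False-positive rate, worked at p = 0.20.**
- Coefficient of the filled covariate: β(1−ρ²)/[1−(1−p)ρ²] = 0.4 × 0.75/0.80 = 0.375.
- Explained variance: 0.375 × 0.80 × 0.4 + 0.05 × 0.20 = 0.13, leaving 0.87.
- SE = √[0.87/(388 × 0.80)] = 0.0529, and z = 0.05/0.0529 = 0.944.
- Rejection rate = Φ(0.944 − 1.96) + Φ(−0.944 − 1.96) = 0.155 + 0.002 = 15.7%.

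**5. Formula against simulation** (N = 388, 1,500-2,000 runs per setting, two runs except at 2%):

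| Missing | Bias, formula | Bias, simulated | False positives, formula | Simulated, null predictor | Simulated, null mediator |
|---|---|---|---|---|---|
| 2% | 0.005 | 0.004-0.006 | 5.1% | 5.2% | 5.1% |
| 5% | 0.013 | 0.013-0.016 | 5.7% | 5.9% | 5.9-6.1% |
| 10% | 0.026 | 0.025-0.029 | 7.7% | 8.4-8.5% | 8.2-9.2% |
| 20% | 0.050 | 0.050-0.053 | 15.7% | 16.7-17.2% | 17.1-17.3% |
| 30% | 0.073 | 0.074-0.076 | 28.3% | 28.6-29.5% | 28.5-30.3% |

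**6. Sensitivity to the assumptions.** With ρ from 0.4 to 0.6, β from 0.3 to 0.5 and n = 390, the simulated rate is 6-14% at 10% missing, 8-37% at 20% and 12-63% at 30%. The top of each range needs the strongest correlation and effect together.

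**7. Missing indicator.** This was simulated for the mediator only, with a binary confounder of effect 0.8 SD whose missingness is three times as likely when it is present. Bias is 0.009, 0.020, 0.039 and 0.053, and the false-positive rate is 5.0%, 6.4%, 11.7% and 16.5%, at 5, 10, 20 and 30% missing.

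**8. Where the rule does no harm.** For 0-30% missing with centre-mean filling, the treatment estimate stays between −0.327 and −0.332 (true value −0.33), with type I error 5.0-5.8%. When C truly modifies the treatment effect and X does not, the treatment-by-X interaction is rejected in 5.3%, 5.5%, 6.4% and 7.0% of runs at 5, 10, 20 and 30% missing.

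**9. Alternative.** Multiple imputation of C with the outcome in the imputation model, at 5-30% missing, gives bias of at most 0.003 and false-positive rates of 4.3-5.9% for both predictor and mediator.

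**The case against.** **Scope.** A reader might infer that the article prescribes this rule for the response and mediation models. It does not say so. The rule is conditional, it refers to the primary and secondary outcome models, and the other two analyses are described separately; the response model even has a different dependent variable. The cited analysis plan may treat them differently. This stands, so coverage is a possible reading and not a stated fact. The reading is still reasonable, because the response model's outcome is change in the primary measure and the article offers no other baseline rule.

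**Effect modification.** A reader might infer that subgroups said to benefit most from CBTp would be artefacts. The interaction results do not support that. What is exposed is the prognostic main effect. The article's covariate list for the response model names no interaction, so main effects are what that model, as described, would report.

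**Missing rates.** No rate is given, and at 2-5% missing the harm is negligible. The article describes breaks, multiple sessions and prioritised measures to limit gaps. This stands, and it is why the point is conditional.

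**Mediation.** Set (a) makes no confounder adjustment and set (c) does not rest on complete measured confounders, so only (b) is concerned. Comparing the three sets also partly probes failure of (b).

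**Other limits.** The response-model covariates are mostly scale scores, so the missing-indicator half matters less. Childhood trauma is first collected at 9 months, so a rule for data missing at baseline does not literally cover it.

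**Conclusion.** The concern holds in a limited form. The rule is right for the randomised comparisons. Its wording leaves room to apply it to the PANSS response model and to mediation set (b), where it would leave part of the confounding in place. At an assumed correlation of 0.5 and effect of 0.4 SD, about 13% of the confounding remains at 10% missing (0.026/0.20) and 25% at 20% missing. False-positive main effects and mediator effects then run at about 8-9% and 17%, against a nominal 5%. At 2-5% missing there is little to correct. These sizes rest on assumed correlations, effects and missing rates. The primary estimate, its type I error and the sample size are unaffected, so this is a minor point about supporting analyses.

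**What to change.** State that centre-mean filling and missing indicators apply only to comparisons between randomised arms. For the response model and mediation set (b), specify multiple imputation of missing covariates, including childhood trauma collected at 9 months. The imputation model should contain the outcome, the mediator where there is one, allocation, site and the other baseline measures, and results should be combined by Rubin's rules. If interactions with allocation are fitted, the imputation model should allow for them. Report the percentage missing for each covariate, so that readers can see whether the issue was material.

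The cost is a sentence or two in the plan and modest extra analysis. Multiple imputation is already among the plan's methods, and neither the sample size nor the data collection changes.
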